### Data management

All researchers and research assistants will attend training seminars before the start of the trial. Researchers at different centers will be requested to follow the same standard operating procedures. Data entry will be completed using the case management system specifically designed for this trial by Jiangsu Famaisheng Medical Technology. To ensure quality and consistency between the source data and the data entered into the system, the data will be entered separately at each center by two research assistants and reviewed by the lead investigator after the completion of each visit. The quality control personnel of the Shanghai Yueyang Integrated Hospital (Shanghai, China) will regularly monitor the data collected at each participating center during the entire study period. The final data will be reviewed and inspected by the Office of State Key Technology R&D Program of the Ministry of Science and Technology of China.

### Statistical methods

All analyses will be performed by applying the SPSS V.21.0, (SPSS Inc., Chicago, IL, USA) statistical software and the data network platform designed by the data management center of Jiangsu Famaisheng Medical Technology. The outcome investigators will be blinded to group allocation. According to the principle of an intention-to-treat analysis, all patients who will be randomized and evaluated according to the efficacy indicators at least once are defined as the full analysis set population, whereas all patients who meet all inclusion and exclusion criteria and deviated from the prescribed dose less than 20% of the regimen are defined as the per-protocol set population. Patients who received treatment one or more times and have at least one safety evaluation will be analyzed in the safety set population. The efficacy measurement will be evaluated mainly by intention-to-treat analysis (full analysis set) and supplemented by per-protocol analysis. The safety evaluation will be analyzed in the safety set population.

If a numerical variable shows normal distribution and the variance is uniform, the statistical description will be expressed as the mean ± standard deviation; the statistical inference will be expressed by the F and S-N-K tests; and the repeated measurement of data analysis of variance will be used for comparison among the groups at multiple time points. In case a numerical variable shows skewed distribution, the median and minimum and maximum values will be used for statistical description; the rank sum test and Nemenyi test will be used for statistical inference, and the generalized estimation equation will be used for comparison among the groups at multiple time points. For categorical variables, the frequency, constituent ratio and rate will be used for statistical description. If the analysis index is unordered, a chi-squared test will be used for statistical inference and, if the analysis index is ordinal, a nonparametric test will be used for statistical inference. The generalized estimation equation will be used for comparison among the groups at multiple time points. Hypothesis testing will be performed using a two-sided test with 95% confidence intervals. A *P* value less than 0.05 indicates statistical significance.

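### The comparison used for each numerical outcome depends on its observed distribution, with no stated criterion and no method for normal data with unequal variances

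*Protocol article*

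**What the plan says.** The rule is in the Statistical methods section of the protocol article and has two branches for numerical variables.

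- **First branch.** The condition is "If a numerical variable shows normal distribution and the variance is uniform". The data are then summarised by mean and standard deviation. Groups are compared on means: "the statistical inference will be expressed by the F and S-N-K tests". Over repeated visits the method is repeated-measures ANOVA.
- **Second branch.** Condition and summary are given together: "In case a numerical variable shows skewed distribution, the median and minimum and maximum values will be used for statistical description". Groups are then compared on ranks: "the rank sum test and Nemenyi test will be used for statistical inference". Over repeated visits the method changes to GEE.

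The section also states "Hypothesis testing will be performed using a two-sided test with 95% confidence intervals". Its threshold for P is worded "value less than 0.05 indicates statistical significance". Categorical variables have their own rule: chi-squared or nonparametric tests, and GEE over time.

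No normality or variance test, cut-off or deciding visit is named, and no named numerical outcome is tied to a method.

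**The concern.** A mean comparison and a rank comparison are different quantities, and a reader of the protocol cannot tell which one will be reported for PASI, BSA, itch or quality of life. The answer depends on data not yet seen and on a judgement whose criterion is unwritten. Two competent analysts could apply the rule to the same data and report different effect measures and P values.

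The rule is also incomplete. Normality and equal variance are both required for the first branch, while the second requires skewness. A variable that is normal but more spread out in one group meets neither condition.

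Finally, the unit of decision is open. The outcomes are measured repeatedly, and the text does not say whether the distribution is judged once per outcome, at each visit, or on pooled data.

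**Working it through.** **1. The rule set out as a table.**

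| Observed feature | Summary | Single time point | Over time | Quantity compared |
|---|---|---|---|---|
| Normal, equal variance | mean, SD | F, S-N-K | repeated-measures ANOVA | means; means |
| Skewed | median, minimum, maximum | rank sum, Nemenyi | GEE | ranks; ordinarily means |
| Normal, unequal variance | none given | none given | none given | undefined |

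The change from means to ranks therefore concerns the single-time-point tests. Over time, neither method is rank-based. (The link for GEE is not stated; an identity link would give differences in means.)

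**2. How often the choice could arise.** From the Outcomes section, with 8 weeks of treatment and 8 weeks of follow-up:

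- PASI: 1 + 8/2 + 8/4 = 7 time points.
- BSA, itch VAS, TCM symptom score, DLQI and PRQoL: 1 + 8/2 + 1 = 6 time points.

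**3. Illustration under assumptions.** The protocol states no figure here to reproduce. Group sizes are the evaluable numbers in the Sample size section (43 in A and B; 72 in C, D and E), and alpha is 0.05 two-sided. Everything else is assumed: Shapiro-Wilk in each group and Levene across groups, each at 0.05. If all pass, the F test is used; otherwise a rank test is used. The uncovered case was given the rank test because some test had to be run. There were 4,000 simulated trials per row, with no true group difference.

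| Data | Mean branch | Neither branch | Null rejected | F and rank disagree on significance |
|---|---|---|---|---|
| Normal, 2 × 43 | 85.7% | 4.0% | 4.5% | 2.1% |
| Normal, 3 × 72 | 82.3% | 3.4% | 4.9% | 2.1% |
| Gamma shape 8, 2 × 43 | 40.3% | 1.9% | 4.7% | 2.4% |
| Gamma shape 8, 3 × 72 | 8.2% | 0.5% | 5.3% | 2.5% |
| Gamma shape 2, 2 × 43 | 0.7% | 0.1% | 5.0% | 3.4% |

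Check on the first column: with truly normal data of equal variance, k groups pass all k + 1 pre-tests with probability of about 0.95^(k+1). That is 0.95³ = 0.857 for two groups and 0.95⁴ = 0.815 for three, in line with the simulation. So these pre-tests alone would send about 14% to 18% of well-behaved trials away from the mean branch.

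Check on the null rejection rate: its Monte Carlo standard error is √(0.05 × 0.95 / 4000) = 0.0034. The departures from 5% are at most about 0.5 percentage points, or 1.5 standard errors.

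**4. Size of the gap.** With normal data, SD 2 against SD 1.2, and 43 per group, 75.8% of trials passed both normality tests and failed Levene, and so had no method. With equal variances the share is 3.4% to 4.0%, which is little more than Levene's own false alarms. How much the gap matters depends on how unequal the variances are.

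**5. If the check were made visit by visit.** With four on-treatment visits, correlation 0.6, two groups of 43 and the same distribution at every visit, the branch differed between visits in 43% of trials with normal data and in 78% with gamma data (shape 8 or 16). These figures apply only if the check is per visit, which the protocol does not say.

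**The case against.** **Switching between visits.** A reader might infer that one outcome will move between means and ranks from visit to visit. The text does not say so. Its condition is on a numerical variable, and each branch has a single method for multiple time points. If the distribution is judged once per outcome, the longitudinal method is defined whenever one of the two branches applies. What stands is that the text permits a per-visit reading and does not exclude it.

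**Type I error.** A reader might infer that choosing the test from the data inflates the false-positive rate. The null simulations do not support this. They cover identically distributed groups only, so they say nothing about a null with unequal variances.

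**Analyst freedom.** A reader might infer that the branch could be picked to suit the treatment effect. The stated trigger is distributional shape and variance, not the effect. What remains is discretion over an unwritten criterion.

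**Scope.** The sample size rests on efficacy rates, and those rates and the relapse rate fall under the categorical rule. This limits the point to the PASI score as a number and to mostly secondary outcomes.

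**Left to the SAP.** Detail of this kind is often held there, and the SAP is not shown. But the article is not silent: it states a rule, and that rule has the gap shown above.

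**Mixed methods in the skewed branch.** A rank test at one visit beside GEE over visits is a mismatch of targets to be explained, not an error in itself.

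**Conclusion.** The point holds for numerical outcomes. The protocol lets the observed distribution and variance decide between comparing means and, at single time points, comparing ranks. It names no criterion or visit for that decision and leaves normal data with unequal variances without a method.

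The consequence is an effect measure and test that are not fixed in advance. On the assumed distributions, F and rank tests reached different conclusions in 2.1% to 3.4% of null trials, and the two-step rule kept its error rate at 4.5% to 5.3%. The share of trials left without a method ran from under 1% to 4% where variances were equal to about 76% with SDs of 2 and 1.2. All these frequencies are illustrations; the protocol supplies neither distributions nor pre-tests. The conclusion itself rests on the wording of the rule and does not need them.

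This should be corrected, but it does not undermine the sample size or the categorical efficacy and relapse comparisons.

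**What to change.** Replace the two-branch rule with one pre-stated longitudinal model for each numerical outcome, used whatever the distribution: change from baseline by group and visit, adjusted for the baseline value, with robust standard errors. This fixes the quantity compared, covers unequal variances and uses baseline values already scheduled for collection. Keep a rank test as a labelled sensitivity analysis. If the SAP already names such a model, align the protocol text with it.

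Reporting quartiles in place of minimum and maximum for skewed data is optional.

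The cost is wording and a little programming, with no change to patients, visits or sample size. The downside is slightly lower efficiency than a rank test if the data are very skewed, which the sensitivity analysis would show.

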### Outcomes

#### Primary outcome

The primary outcome in this trial is evaluation of the efficacy and incidence of relapse in response to sequential treatment with integrated Chinese and western medicines during the treatment and follow-up periods. Relapse is defined as a PASI score exceeding the baseline score at the time of enrollment or development of new pustules or erythroderma [27]. PASI will be assessed at baseline, at 2-week intervals during the treatment period, and at 4-week intervals throughout the follow-up period.

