### Sample size

The sample size for this study was calculated based on the expected value of the efficacy based on the results from previous studies [17, 28]. The efficacy rates for groups A, B, C, D and E were 30.0%, 59.0%, 73.0%, 55% and 88.0%, respectively. The significance level (alpha) was set at 0.05 and the statistical power was 80%. Based on our calculation using the PASW statistical software (V.18.0), a sample size of 43 patients was required for groups A and B and 72 patients for groups C, D and E. However, considering a potential 25% loss of patients during follow-up, we adjusted the total sample sizes of groups A and B to 54 patients and that of groups C, D and E to 90 patients.

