### Assignment of interventions: allocation

#### Sequence generation

Eligible patients with mild-to-moderate or severe psoriasis will be enrolled at each of the six participating institutions and will be randomized separately. During their second visit, patients with mild-to-moderate psoriasis will be randomly assigned to either group A or group B in a 1:1 ratio, while those with severe psoriasis will be randomly assigned to group C, group D or group E in a 1:1:1 ratio. Randomization will be performed using a computer-generated random assignment sequence through the central layering and block randomization method of SAS software (V.9.4).

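### The tests named for single-time-point comparisons use neither baseline values nor the randomisation strata, which costs some precision, mainly for the continuous outcomes

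*Protocol article*

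**What the plan says.** The Statistical methods section of the protocol article assigns tests by type of variable.

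- Normal with uniform variance: "the statistical inference will be expressed by the F and S-N-K tests".
- Skewed: rank sum and Nemenyi tests.
- Categorical: "If the analysis index is unordered, a chi-squared test will be used for statistical inference", with a nonparametric test for ordinal data.
- Several time points: repeated-measures ANOVA for normal data, generalised estimating equations (GEE) otherwise.

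No baseline covariate, centre term or stratification factor is named for any of them.

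Under Sequence generation, patients are enrolled at six institutions and allocated "through the central layering and block randomization method of SAS software". The strata are not listed; centre is the most plausible reading. Under Primary outcome, "PASI will be assessed at baseline" and then repeatedly. Under Secondary outcomes, BSA, PGA, pruritus VAS, TCM symptom score, DLQI and PRQoL also have baseline assessments.

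**The concern.** When randomisation is stratified and the strata predict outcome, an analysis that leaves them out keeps between-stratum variation in the error term, so standard errors come out somewhat too large. A test that leaves out the baseline value of the same scale also treats predictable variation as noise, and chance baseline imbalance stays in the estimate.

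The choice between the F and rank families also rests on how the trial data turn out to be distributed. The method, and with it the quantity compared (means or ranks), is therefore not settled for each outcome in advance. What is at stake is wider intervals than the collected data allow, and a primary analysis that is not fully fixed.

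**Working it through.** **Inputs from the Sample size and Statistical methods sections.** Rates: "The efficacy rates for groups A, B, C, D and E were 30.0%, 59.0%, 73.0%, 55% and 88.0%, respectively". Evaluable numbers: "a sample size of 43 patients was required for groups A and B and 72 patients for groups C, D and E". Alpha is 0.05, target power 80%, tests two-sided. There are six centres (Study setting).

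**Assumed inputs, because the article gives none.** Baseline-to-outcome correlation r = 0.3 to 0.6; between-centre SD 0 to 0.8 on the logit scale; baseline effect 0 to 0.8 log-odds per SD.

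**Step 1: the plan's own sample sizes.** For A versus B, the unpooled formula n = (1.960 + 0.842)² × [p₁(1−p₁) + p₂(1−p₂)] / (p₁−p₂)² gives 7.849 × (0.2100 + 0.2419) / 0.0841 = 42.2, so 43, as stated. The pooled formula gives 45. The 72 per group for C, D and E is not reproduced: the pooled two-sided formula gives 111 (C–D), 109 (C–E) and 29 (D–E), and a three-group omnibus chi-squared test needs 36. Unadjusted power, pooled two-sided:

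| Comparison | n per group | Power |
|---|---|---|
| A–B | 43 | 78% |
| C–D | 72 | 62% |
| C–E | 72 | 62% |
| D–E | 72 | over 99% |
| C, D, E omnibus | 72 | 98% |

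**Step 2: continuous outcomes.** With outcome variance σ², ANCOVA leaves σ²(1−r²). Against a comparison of post-treatment scores the variance ratio is 1−r². A change score has variance 2σ²(1−r) if baseline and outcome variances are equal, so the ratio against it is (1−r²)/[2(1−r)] = (1+r)/2.

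| r (assumed) | ANCOVA / post-score | Equivalent sample-size factor 1/(1−r²) | 80% power becomes | ANCOVA / change score |
|---|---|---|---|---|
| 0.3 | 0.91 | 1.10 | 84% | 0.65 |
| 0.5 | 0.75 | 1.33 | 90% | 0.75 |
| 0.6 | 0.64 | 1.56 | 94% | 0.80 |

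The fourth column is Φ(2.802/√(1−r²) − 1.960). At r = 0.5, 2.802/0.866 − 1.960 = 1.275, so 90%.

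**Step 3: the binary efficacy rate, by simulation.** Change in power against the plain chi-squared test, in percentage points, over the assumed ranges:

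| Comparison | Cochran-Mantel-Haenszel (CMH) by six centres | Logistic with baseline covariate |
|---|---|---|
| A–B, n = 43 | −1 to +2.5 | −0.5 to +4.6 |
| C–D, n = 72 | 0 to +3 | −0.4 to +6.6 |
| C–E, n = 72 | −1 to +2 | −2 to +2 |

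The top of each range belongs to the strongest assumed predictor. The highest adjusted power for C–D or C–E at n = 72 is about 67%.

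**Step 4: validity.** With both groups at 73% and n = 72, chi-squared rejects 5.1%, 5.0% and 4.0% of the time at centre SD 0, 0.5 and 0.8; CMH rejects 5.0%, 5.2% and 4.8%. The unadjusted test does not inflate type I error, and is mildly conservative when centres differ strongly.

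**Step 5: sparseness after adjustment.** Group E at 88% response and n = 72 has 72 × 0.12 = 8.64 expected non-responders. Spread equally over six centres, that is 8.64 / 6 = 1.4 each.

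**The case against.** The strongest reply is that covariate lists usually sit in the statistical analysis plan, which is not shown, and that the article nowhere excludes baseline or centre. This stands for the repeated-measures ANOVA and GEE: their terms are unspecified, and both could carry baseline and strata. It is weaker for the single-time-point tests, because the article names them. Rank sum, Nemenyi and plain chi-squared have no place for a covariate, so an adjusted analysis would depart from the published text.

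Three stronger readings are tempting, and the document does not support them.

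- **That the plan ignores baseline PASI.** Relapse is defined against the enrolment score, PASI 75 is a percentage reduction, and several secondary outcomes are improvements. Baseline already enters these definitions. Defining an outcome from baseline is still not adjusting for it, as the change-score column in the working shows.
- **That the trial is short of power and adjustment would rescue it.** Only C–D and C–E are clearly short at n = 72; A–B is close to target, and D–E and the omnibus test are well above it. The shortfall comes from the figure of 72, and adjustment leaves both comparisons at or below about 67%. Nor would the severe-disease comparisons all gain most: C–E gains less than A–B.
- **That the r² gain applies to the endpoint used for sizing.** It applies to continuous scores only. The trial was sized on rates, which go to chi-squared, and there the change is small and sometimes at or below zero.

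Stratification by centre also remains an inference from the wording, not a stated fact.

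**Conclusion.** The point holds as one of precision, not validity. The single-time-point tests are fixed in unadjusted form although the design stratifies and the baselines are collected. For continuous outcomes, adjustment would cut variance by 9% to 36% against a post-treatment comparison, or by 35% to 20% against a change-score comparison, for r from 0.3 to 0.6. The article gives no correlation, and the change-score figures also assume equal variances. For the binary efficacy rate the effect is roughly −2 to +7 power points under the assumed centre spread and baseline effect. The change is worth making because it is nearly free, but it is no remedy for the C–D and C–E sample size.

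**What to change.** - **Continuous outcomes:** prespecify ANCOVA, or a mixed model over visits, with the baseline value and the randomisation strata as primary, whatever a normality check on the trial data shows.
- **Binary efficacy rate:** prespecify either a CMH test stratified by the randomisation strata, or logistic regression with baseline PASI and strata, reported as a standardised risk difference with 95% confidence interval.
- **Strata and model terms:** list the strata used in randomisation, and state the terms of any repeated-measures ANOVA or GEE that is kept.
- **Unadjusted tests:** keep them as sensitivity analyses.

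The cost is wording, since PASI and the secondary scales are already measured at baseline and centre is known. The one downside is sparse centre cells where response is high, as in group E. Logistic regression with centre terms may then be unstable, so prespecify CMH or a rule for pooling small centres.

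### For numerical outcomes that pass the normality check, repeated-measures ANOVA does not fit a full analysis set that requires only one evaluation

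*Protocol article*

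**What the plan says.** All of the relevant analysis text is in the Statistical methods section of the protocol article.

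- **Population.** The section states that "all patients who will be randomized and evaluated according to the efficacy indicators at least once are defined as the full analysis set population". Efficacy is judged mainly on this set, with a per-protocol analysis as support.
- **Method over time, first branch.** The condition is "If a numerical variable shows normal distribution and the variance is uniform". If it is met, "the repeated measurement of data analysis of variance will be used for comparison among the groups at multiple time points".
- **Method over time, other branches.** For skewed numerical variables and for categorical variables, "the generalized estimation equation will be used for comparison among the groups at multiple time points". Unordered categorical outcomes are also compared by chi-squared test.
- **Software.** "All analyses will be performed by applying the SPSS V.21.0". The procedure within SPSS is not named.

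The Sample size section inflates the group sizes "considering a potential 25% loss of patients during follow-up". The section on who takes informed consent asks withdrawing patients for one closing assessment of efficacy and safety. It does not say that they continue with the remaining scheduled visits.

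**The concern.** Classical repeated-measures ANOVA needs a value at every modelled visit. A patient seen at baseline and week 2 who then withdraws belongs to the full analysis set but cannot enter this model unless the missing values are filled in. For outcomes on this branch, the plan names a population and a method that cannot both be applied as written.

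There are two consequences. First, scores already collected from partly observed patients would be discarded. Second, whether a numerical outcome is analysed on all available patients or only on those with complete profiles would depend on a distributional check of the trial data, because the skewed branch uses a method that keeps available visits. The analysed population should not depend on that check.

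The outcomes that could fall on this branch are the PASI score taken as a number, BSA, the pruritus VAS and the DLQI.

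**Working it through.** **Inputs**

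- Sample size section: 43 (A, B) and 72 (C, D, E) required per group; 54 and 90 after allowing for 25% loss. Total: 2 × 54 + 3 × 90 = 378.
- Primary outcome section: PASI at baseline, every 2 weeks over 8 weeks of treatment (weeks 2, 4, 6, 8) and every 4 weeks over 8 weeks of follow-up (weeks 12, 16). That is seven assessments, six of them after baseline.
- Secondary outcomes section: the other scores at baseline, weeks 2, 4, 6, 8 and the end of follow-up. That is six assessments, five of them after baseline.

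**Step 1: the plan's own figures.** 43 × 1.25 = 53.75, rounded up to 54, and 72 × 1.25 = 90. Both reproduce, so the 25% is the allowance actually used.

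**Step 2: complete profiles at the planned loss, all visits to week 16 modelled, no imputation.** Patients kept = N × (1 − 0.25).

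- A, B: 54 × 0.75 = 40.5, about 40 per group.
- C, D, E: 90 × 0.75 = 67.5, about 67 per group.
- Whole trial: 378 × 0.75 = 283.5, about 283.

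A model that uses available visits could draw on up to 54 and 90 per group.

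**Step 3: lower if visits are also missed intermittently.** The article gives no missed-visit rate, so m is an assumption, taken as independent across visits. Share kept for PASI = 0.75 × (1 − m)^6.

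| m | Share kept | Of 54 | Of 90 |
|---|---|---|---|
| 0 | 75% | 40 | 67 |
| 2% | 66% | 36 | 60 |
| 3% | 62% | 34 | 56 |
| 5% | 55% | 30 | 50 |

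The other scores have five post-baseline visits. At m = 2% the share is 0.75 × 0.98^5 = 68%, and at m = 5% it is 0.75 × 0.95^5 = 58%.

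**Step 4: higher if only treatment visits are modelled.** The article does not say which visits enter the model. Let f be the assumed share of the loss that falls after week 8, with no intermittent gaps. Share kept = 1 − 0.25 × (1 − f).

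- f = 0: 75% (40.5 of 54; 67.5 of 90).
- f = 0.5: 87.5% (47.25 of 54; 78.75 of 90).
- f = 1: 100%.

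**Step 5: bias.** No input in the article fixes its size or sign. A small simulation with assumed values (25% loss per group, related to response in one group only) gave a group difference of −1.20 in completers against −1.19 with full data. It gave every patient within a group the same underlying rate of improvement, so response-related loss had little to select on. It settles nothing in either direction.

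**The case against.** The strongest reply is that the ANOVA is only one branch. It applies when a numerical outcome is normal with equal variance. PASI may well be skewed, since enrolment is capped at 15% BSA and efficacy rates of up to 88% are expected. Skewed and categorical outcomes go to generalized estimating equations, which keep available visits. This stands and limits the point to numerical outcomes that pass the check.

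A reader might infer that the trial's main intention-to-treat comparison turns into a completers analysis. The documents do not support that. The sample size rests on efficacy rates, and relapse is an incidence. Both are categorical and take the chi-squared or estimating-equation route.

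A reader might also take 25% as a minimum for patients dropped. The article calls it a potential loss, and part of it may fall after week 8. The reminders described under adherence may reduce it further.

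A reader might infer that the comparison is biased because patients leave for lack of effect or adverse reactions, differently by arm. That is possible, but the article neither says it nor gives figures from which to compute it.

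Imputation could reconcile the method with the population, and an analysis plan that is not shown may specify it. For that reason the absence of a missing-data rule is not criticised here. Requiring one evaluation for the full analysis set is a common convention and is not criticised either.

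What the reply does not remove is that the article itself names a method that, in its classical form, cannot use all of the patients it names as its main population.

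**Conclusion.** The point holds in a limited form. For numerical outcomes that meet the normality and equal-variance condition, the named longitudinal method conflicts with the full analysis set unless missing visits are imputed.

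At the planned 25% loss, with all visits to week 16 modelled, about 40 of 54 and 67 of 90 patients per group would enter the comparison. This rests on three assumptions: the classical form of the ANOVA, no imputation, and loss at the planning level. Intermittent gaps lower the counts and a model of treatment visits only raises them. The 43 and 72 in the Sample size section are no benchmark here, because they were derived for rates.

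The efficacy and relapse rates are unaffected, and no claim of bias in a given direction is made. The mismatch is worth correcting because a better method is available at little cost.

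**What to change.** For numerical outcomes on the normal, equal-variance branch, replace repeated-measures ANOVA with a likelihood-based mixed model for repeated measures. Fit it separately in the mild-to-moderate part (A, B) and the severe part (C, D, E). Include group, visit, group × visit and the baseline value, with an unstructured covariance across post-baseline visits. Use all observed visits of every full-analysis-set patient. State which visits enter the model.

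With baseline as a covariate, a patient who has only a baseline value still contributes nothing to the comparison. The text should therefore say whether the single qualifying evaluation must be post-baseline.

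The planned SPSS provides this model as MIXED, so no new software or data are needed. The cost is a change of wording and slightly more analysis work. An unstructured covariance for six post-baseline PASI visits has 6 × 7 / 2 = 21 parameters, so a simpler fallback should be named in case the fit fails. The model also relies on data being missing at random given the observed values, and the text should state that assumption.

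Extending the estimating equations already named to these outcomes would also keep available visits. In their standard form, however, they need a stronger assumption about why data are missing, so the mixed model is the better choice.
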